# The effect of internet-administered support (carer eSupport) on preparedness for caregiving in informal caregivers of patients with head and neck cancer compared with support as usual: a study protocol for a randomized controlled trial

**DOI:** 10.1186/s12885-024-12273-y

**Published:** 2024-04-18

**Keywords:** Head and neck cancer, Informal caregivers, Internet-administered support, Preparedness for caregiving, Caregiver burden, Quality of life.

## Abstract

**Background:**

Informal caregivers (ICs) of patients with cancer provide essential and mainly uncompensated care. A self-perceived preparedness to care for the patient is associated with a lower caregiver burden, described as the extent to which caregiving is perceived as having adverse effects on IC functioning and well-being. ICs’ well-being is associated with patient-perceived quality of care, suggesting that interventions to optimize ICs’ health are essential in order to improve patient care. Head and neck cancer (HNC) is the seventh most common malignant disease in the world. The disease and its treatment have a significant negative impact on the patient’s health and quality of life. Symptoms usually interfere with swallowing, food and fluid intake, breathing, speaking, and communication. ICs frequently manage patients’ symptoms and side effects, especially problems related to nutrition and oral pain, without being properly prepared. Carer eSupport is an Internet-administered intervention, based on focus group discussions with ICs, developed in collaboration with ICs and healthcare professionals, tested for feasibility, and deemed feasible. This study protocol outlines the methods of investigating the effects of Carer eSupport plus support as usual (SAU) on self-reported preparedness for caregiving, caregiver burden, and well-being in the ICs of patients with HNC, compared with ICs receiving SAU only.

**Methods and analysis:**

In this randomized controlled trial, 110 ICs of patients with HNC, undergoing radiotherapy combined with surgery and/or medical oncological treatment, will be randomized (1:1) to Carer eSupport plus SAU or SAU only. Data will be collected at baseline (before randomization), post-intervention (after 18 weeks), and 3 months after post-intervention. The primary outcome is self-reported preparedness for caregiving. Secondary outcomes are self-reported caregiver burden, anxiety, depression, and health-related quality of life. The effect of Carer eSupport plus SAU on preparedness for caregiving and secondary outcomes, compared with SAU only, will be evaluated by intention to treat analyses using linear regression models, mixed-model regression, or analysis of covariance.

**Discussion:**

If proven effective, Carer eSupport has the potential to significantly improve ICs’ preparedness for caregiving and their wellbeing, thereby improving patient-perceived quality of care and patient wellbeing.

**Trial registration:**

ClinicalTrials.gov; NCT06307418, registered 12.03.2024 (https://clinicaltrials.gov/search? term=NCT06307418).

## Background

Informal caregivers (ICs) are still an unnoticed workforce in the care of patients with cancer. They are commonly family members, relatives, or close friends who provide essential and mainly uncompensated care. ICs are often thrust unprepared into the caring role, a role that is often physically, emotionally, and socially demanding and entails significant time and energy [1, 2]. Self-perceived readiness and capacity, reflecting the perceived preparedness to care for the patient, is associated with a lower caregiver burden [3]. Lack of preparedness often includes lack of knowledge and skills, concerns about one’s capacity for caring, distress, and feelings of abandonment by healthcare [4]. Caregiver burden may be described as the extent to which caregiving is perceived as having adverse effects on the caregiver’s emotional, social, financial, physical, and spiritual functioning [5]. ICs’ well-being is associated with patient-perceived quality of care, suggesting that interventions to optimize ICs’ health are essential in order to improve patient care [6].

Head and neck cancer (HNC) is the seventh most common malignant disease in the world and comprises a diverse group of cancer tumors in the upper aerodigestive tract [7]. The median age at diagnosis is approximately 60 years. However, incidence is increasing in younger persons diagnosed due to more cases of oropharyngeal squamous cell carcinoma associated with human papillomavirus (HPV). The prognosis of HNC varies considerably depending on the site of involvement and stage at diagnosis, among many other variables. The 5-year overall survival rate for patients with HNC is 70–90% in patients with stage I–II tumors and < 50% in patients with stage III–IV tumors [8]. Patients with HPV-associated HNC tend to have a better prognosis than do patients with non-HPV-associated HNC. The treatment of HNC differs according to the site of involvement, stage of disease, and comorbidity, but commonly includes single- or combined-modality treatment with external beam radiotherapy, surgery and/or chemotherapy, or targeted therapy [8]. The disease and treatment have a significant negative impact on the patient’s physical, social, and emotional health and overall quality of life. Symptoms usually interfere with vital functions such as swallowing, food and fluid intake, breathing, speaking, and communication, as well as altering facial appearance [9, 10]. ICs frequently manage patients’ symptoms and side effects, especially problems related to nutrition and oral pain, including tube feeding and pain management. Responsibility for navigating the healthcare system and arranging healthcare appointments are other tasks that often fall to the IC’s lot [11, 12]. Many ICs of patients with HNC prioritize the needs of the patient and set aside their own self-care care needs, which may lead to deteriorated IC health [1, 13]. Thus, both ICs’ and patients’ lives, as well as their relationships, may be severely affected by the cancer diagnosis.

Systematic reviews suggest that interventions for ICs of patients with cancer, including Internet-administered interventions, may increase self-efficacy and preparedness for caregiving, decrease caregiver burden, and/or improve well-being in ICs [14–18]. Studies of online interventions are still sparse [14] and limited in quality and generalizability; we have identified only one Internet-administered intervention (a pilot study, *n* = 38) addressing the ICs of patients with HNC [19]. Ugalde et al. [20] explored the potential of 26 IC interventions to be implemented in practice. Only two of the included studies involved ICs in developing the intervention, only two addressed whether the intervention was appropriate for clinical care, and no study discussed intentions or actions to facilitate implementation in routine cancer care. Thus, existing interventions lack the necessary components to bridge the gap between research and clinical care. We want to reduce the gap between scientific evidence and practical application, ultimately enhancing health outcomes for both ICs and patients by exploring the potential of Internet-administered interventions designed with ICs’ input and emphasizing the importance of application usability to cater to a diverse range of technological proficiencies and maintain long-term engagement [21, 22].

### The Carer eSupport project: development of a usable internet-administered intervention

Our multidisciplinary research group includes expertise in HNC clinical care, the caring sciences, and the human–computer interaction science, and is experienced in research into the development and evaluation of Internet-administered support: the group is unique and well equipped to further our knowledge of important aspects of clinically relevant and usable Internet-administered support interventions. We have developed a complex intervention [23] consisting of Internet-administered support (“Carer eSupport”) for ICs of patients with HNC [24]. The first steps were to strengthen the relevance and usability of Carer eSupport, to test the feasibility of Carer eSupport, and to test the recruitment procedures (more clearly described in “Methods”). In our initial focus groups with the ICs of patients with HNC, many expressed a need for emotional and practical support from their social network and healthcare [11, 25]. They commonly changed their work and home routines to prioritize caring for the patient, and some neglected their health needs to attend to the needs of the patient. The ICs’ opinions regarding Internet-administered support stressed the importance of trustworthy information, tailored especially to the ICs of patients with HNC, concerning HNC, cancer treatment, caregiving, their well-being, and daily life activities. The possibility of sharing experiences with and learning from peer ICs and healthcare professionals in discussion forums and real-time video meetings was also highlighted as essential to Carer eSupport. Subsequent focus groups with healthcare professionals having expertise in HNC care [25], conducted to facilitate the possible future implementation of Carer eSupport in clinical care, corroborated the ICs’ experiences and perceived needs for support. These professionals believed that current information on the Internet about HNC and its treatment is too general. However, they also emphasized that the experience of symptoms and side effects is individual and may differ substantially between patients. This clarifies that Internet-administered information is a complement to, and not a substitute for, individualized information from healthcare professionals responsible for patient care [26]. Both ICs and healthcare professionals stressed that online discussions among peer ICs need to be monitored by experts to prevent the spread of incorrect information.

This study protocol outlines the methods of investigating the effects of Internet-administered Carer eSupport plus support as usual (SAU) on self-reported preparedness for caregiving, caregiver burden, and well-being in the ICs of patients with head and neck cancer, compared with ICs receiving only SAU.

## Methods

### Design

The RCT constitutes the third step in developing and evaluating this complex intervention, which is based on the United Kingdom Medical Research Council’s complex interventions framework [23]. The design and methods of the two initial steps of the project have been published elsewhere [24]. The project is being conducted in accordance with the Helsinki Declaration [27], has been approved by the Swedish Ethical Review Authority (Dnr 2020–04650/2022-06520-02/2023-02005-02), and has been registered in ClinicalTrials.gov (registration number: NCT06307418). This protocol complies with the Standard Protocol Items: Recommendations for Interventional Trials guidelines on writing protocols [28]. The software packages used for delivering Carer eSupport, collecting data, randomization, and storing research data are installed on encrypted and secured servers at Uppsala University, in accordance with the university’s information security regulations. Personal data will be stored and secured in a separate database, which is compliant with the European Union General Data Protection Regulation (GDPR, 2016/679).

### Hypotheses

The main hypothesis is that ICs receiving Carer eSupport plus SAU (described below) will report greater preparedness for caregiving than will ICs receiving SAU only. Secondary hypotheses are that ICs who receive Carer eSupport plus SAU will report a lower caregiver burden and better self-perceived health, including less anxiety and depression, than will ICs receiving SAU only.

### Sample

One hundred and ten ICs of patients with HNC will be recruited at ear, nose, and throat (ENT), oncology, and radiotherapy clinics at four Swedish university hospitals. The IC will only be approached if the patient gives written consent. The recruitment will run for ten months, starting in summer 2024.

#### Inclusion criteria

The patients with HNC and ICs will be adults (> 18 years). The patients will be about to start or have undergone at most five radiotherapy treatment sessions/fractions. Radiotherapy may be combined with surgery and/or medical oncological treatment. The IC will be identified as such by the patient and may be a spouse/partner, another family member, or a friend.

#### Exclusion criteria

ICs and patients who do not understand and read Swedish or suffer from cognitive impairment will be excluded. In addition, ICs who are deemed to need support or treatment that cannot be provided by Carer eSupport (e.g., psychotherapy or medication) will be excluded and referred to appropriate healthcare.

### Power analysis

The estimated sample size is based on a study by Holm et al. [29], who evaluated the effect of psycho-education on preparedness for caregiving, using the Preparedness for Caregiving Scale as the primary outcome. According to that study, a total sample size of 55 ICs is required to obtain 80% power to detect a medium-size effect on preparedness using multiple regression analysis (f2 = 0.15, alpha = 5%) [29]. However, based on our earlier Internet-administered studies, high attrition (≤ 50%) may be expected [30, 31] due to the ICs’ strained situation and possible unfamiliarity with computers and/or mobile devices. Therefore, we plan to include 110 ICs, i.e., 55 receiving Carer eSupport plus SAU and 55 receiving SAU only.

### Randomization

ICs will be randomized to Carer eSupport plus SAU or SAU only (ratio 1:1). The randomization will be computer generated and done within the Internet-administered data collection tool, after completion of the baseline questionnaires.

### Development and feasibility testing of carer eSupport

The Social Cognitive Theory (SCT) [32] and the Unified Theory of Acceptance and Use of Technology (UTAUT) [33] constitute the theoretical framework for Carer eSupport. Self-efficacy, a core construct of SCT [32], is conceptualized as a person’s self-perceived capacity to perform in a particular situation. For the ICs of patients with HNC, it may be assumed that ICs with a high self-efficacy regarding their capacity to care for the patient also perceive high preparedness for caregiving, and therefore will be more successful in caregiving. The SCT also states that individuals learn from social interactions with others, which is made possible in Carer eSupport discussion forums and real-time video meetings (described below). The UTAUT is a technology acceptance theory comprising the key constructs of performance expectancy, effort expectancy, social influence, and facilitating conditions. In the context of Carer eSupport, these constructs refer to whether ICs believe that Carer eSupport can improve their preparedness for caregiving, the efforts they expect when using Carer eSupport, whether essential persons in their surroundings believe that they should use Carer eSupport, and organizational or technical enablers of and barriers to using Carer eSupport.

We used the theoretical framework, the results of focus group discussions (presented in “Background”), and existing scientific evidence to develop the first version of Carer eSupport in collaboration with healthcare professionals and an expert group including the ICs of patients with HNC. Thirty-two ICs of patients with HNC have tested that first version in a feasibility study conducted in 2023. The ICs had access to Carer eSupport for one month, after which they completed the questionnaires that will be used in the RCT (described below). Nineteen of 32 ICs took part in individual interviews after 1–2 months regarding their experience of Carer eSupport and their opinions about how it could be improved. Data from the feasibility study were analyzed according to our predefined feasibility criteria [24], i.e., ≥ 45% gave written consent, ≥ 50% used Carer eSupport, < 30% discontinued participation, ≥ 50% completed the questionnaires, and whether Carer eSupport was considered acceptable, relevant, and usable according to the interviews. The analysis revealed that 32 of 52 approached ICs (62%) gave written consent, 22 of them (69%) used Carer eSupport, according to logged “clicks” on text and video files, 16 (50%) completed the questionnaires, and nine (28%) discontinued participation. The ICs experienced Carer eSupport as relevant, helpful, and usable, according to the interviews. However, they gave suggestions for improving Carer eSupport, for example, adding content and improving website design, which have been implemented accordingly. In addition, important knowledge of the recruitment and data collection procedures was obtained. One important finding was the ICs’ experience that the data collection included too many questions. That led to the decision to exclude a fatigue scale since fatigue is the least significant outcome measure compared with our remaining outcome measures, according to previous research [11, 13]. The conclusion was that Carer eSupport and the associated research procedures are feasible after the improvements and can be employed in the RCT. The feasibility study will be reported in detail elsewhere.

### Carer eSupport evaluated in the RCT

Carer eSupport is additional to SAU (described below) and will last for 18 weeks for each IC randomized to the intervention. They will be informed that their access to Carer eSupport will be ended in one week, after 17 weeks via SMS and e-mail. The content of Carer eSupport covers HNC and its treatment, patients’ commonly experienced physical and emotional symptoms, side-effects of treatment, everyday caregiving tasks, self-care, and guided self-help for ICs’ emotional distress (Table 1). The functionality includes text in the form of web pages and PDFs, lectures with voice-over, videos, a question-and-answer (Q&A) section including functionality to pose questions to experts, a monitored discussion forum, and functionality for real-time video meetings. Clinical experts (Table 1) will participate in regular video meetings with ICs and answer questions from ICs in the discussion forums and the Q&A section. PDFs, lectures, and videos will be downloadable.

**Table 1 Tab1:** The content, functionality and clinical expertise involvement in Carer eSupport, Internet-administered support directed to informal caregivers (ICs) of patients with head and neck cancer

Content	Functionality	Clinical expertise involvement
Head and Neck Cancer (HNC) Human papillomavirus (HPV)	Text Lecture Discussion Forum Real time video meeting	HNC specialist, physician HNC specialist, nurse
Treatment of HNC - Surgery - Radiotherapy - Chemotherapy - Schedule for post-treatment follow-ups	Text Lecture Film Discussion Forum Real time video meeting	HNC specialist, physician HNC specialist, nurse
Side effects of treatment - Nutrition - Oral hygiene - Voice and Speech - Pain - Fatigue - Physiotherapy - Sexuality - Skin - Lymphedema	Text Lecture Discussion Forum Real time video meeting	Dietician Dental hygienist Speech therapist Pain Medicine Specialists HNC specialist, physician HNC specialist, Nurse Physiotherapist Sexologist
Medical devices - Peripherally Inserted Central Catheter (PICC) line, Subcutaneous Venous Port, and Peripheral Venous Catheter (PVC) - Nasogastric tube, Percutaneous endoscopic gastrostomy (PEG), and Radiologically inserted gastrostomy (RIG)	Text Lecture Discussion Forum Real time video meeting	HNC specialist, physician HNC specialist, nurse Dietician
Emotional reactions patients - Crisis - Anxiety - Depression	Text Lecture Discussion Forum Real time video meeting	Healthcare counsellor Psychologist
Emotional reactions ICs - Crisis - Anxiety - Depression - Sexuality	Text Lecture Discussion Forum Real time video meeting	Psychologist Healthcare counsellor Sexologist
Self-Care for ICs - Fatigue - Sleep - Physical activity - Daily life practical issues	Text Lecture Discussion Forum Real time video meeting	HNC specialist, nurse Physiotherapist Healthcare counsellor
ICs own story	Lecture	ICs

### Support as usual (SAU)

SAU comprises the possibility of ICs contacting a specified nurse with expertise in HNC, at the ENT or oncology clinic, to ask for support. These contacts are commonly restricted to occasional appointments and/or phone calls. Healthcare counselors at the clinics are also available for ICs on request. Also, the Swedish healthcare system is always responsible for recognizing the need to support the children (< 18 years old) of patients with cancer; nurses, physicians, and healthcare counselors commonly coordinate that support within Swedish cancer care. Support groups providing emotional and social support to the ICs of patients with various cancer diagnoses may also be arranged on occasion at the clinics. However, Internet-administered support, tailored to the needs of ICs of patients with HNC, is not available in SAU.

### Procedure

#### Recruitment

Nurses at the ENT, oncology, and radiotherapy clinics will identify and screen patients according to the inclusion and exclusion criteria (Fig. 1). A clinical or research nurse will approach an eligible patient in person or by telephone, to inform them about the study, ask for consent to contact an IC (suggested by the patient), and ask whether medical data about the HNC diagnosis and treatment can be collected from the medical record. After the patient has given oral and written informed consent, the clinical or research nurse will contact the IC in person by telephone or email to set a time for the IC to receive information about the study. The information will be given in person, via telephone, or via a video meeting. ICs who give oral and written informed consent will be provided with the web address to the internet-administered questionnaires, a user ID, and a preliminary password. Participating ICs will be randomized to Carer eSupport plus SAU or SAU after the baseline assessment is completed. ICs who are randomized to Carer eSupport plus SAU will be provided with the web address, a user ID, and a preliminary password to Carer eSupport.

**Fig. 1 Fig1:**
[figure not shown]
Flow-chart of planned enrollment of patients and informal caregivers (ICs), allocation and follow-up of informal caregivers, and analysis

#### Allocation and follow-up

Randomized ICs will be allocated to Carer eSupport or SAU for 18 weeks, corresponding to the entire primary treatment period and an additional eight weeks, when the acute side effects are expected to diminish. Follow-up assessments (see “Data collection,” below) are scheduled for 18 weeks after randomization (post-intervention), and three months after post-intervention.

#### Internal pilot study: feasibility testing

ICs included in the internal pilot study will be informed accordingly and asked to provide oral and written consent, using the same procedures as described above. The internal pilot study will comprise a feasibility analysis after the randomization of 30 ICs to confirm the feasibility of the procedures and the updated version of Carer eSupport, completed after the previous feasibility study (described above). The analysis will concern the consent to participate rate, ICs’ use of Carer eSupport according to logged data, and attrition rate one month after randomization. If the progression criteria for feasibility are met [24], i.e., if ≥ 45% give written consent, ≥ 50% use Carer eSupport, and < 30% discontinue participation, the pilot study and the included ICs will seamlessly proceed to the main RCT. However, if the criteria are not met, the recruitment will be ended. ICs randomized to Carer eSupport plus SAU will be able to continue to use Carer eSupport for the entire 18-week period if the recruitment is ended, but they will not be asked to complete the follow-up assessments (see “Data collection”).

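### The internal pilot is read at one month on consent, use and discontinuation only, so it cannot check the 50% endpoint completion on which the sample size of 110 depends

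*Protocol article*

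**What the plan says.** All references are to the protocol article.

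- **Internal pilot study: feasibility testing.** "The internal pilot study will comprise a feasibility analysis after the randomization of 30 ICs". Its purpose is to confirm that the procedures and the updated intervention are feasible. On content and timing: "The analysis will concern the consent to participate rate, ICs’ use of Carer eSupport according to logged data, and attrition rate one month after randomization". The progression criteria are then listed in full: consent at least 45%, use at least 50%, discontinuation below 30%. If they are not met, recruitment ends.
- **Development and feasibility testing of carer eSupport.** The feasibility study cites the same source for its criteria, but its list contains one more quantitative item: "< 30% discontinued participation, ≥ 50% completed the questionnaires". The result, after one month of access, was "16 (50%) completed the questionnaires, and nine (28%) discontinued participation".
- **Power analysis.** "a total sample size of 55 ICs is required to obtain 80% power to detect a medium-size effect on preparedness using multiple regression analysis", with f² = 0.15 and alpha 5%. Then "high attrition (≤ 50%) may be expected", and so "we plan to include 110 ICs, i.e., 55 receiving Carer eSupport plus SAU and 55 receiving SAU only".
- **Allocation and follow-up; Data collection.** Outcomes are collected at baseline, at 18 weeks, and three months after that. Nothing is collected at one month.
- **Randomization.** Caregivers are randomized only once the baseline questionnaires are complete.

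**The concern.** The internal pilot is the only check before the full trial for which the article sets criteria. Its sample-size premise is that at least half of the randomized caregivers will supply endpoint data. The one criterion that addressed questionnaire completion in the feasibility study is missing from the pilot. At one month it could not be measured anyway, because the first follow-up questionnaire falls due at 18 weeks. Baseline completion cannot stand in, since every randomized caregiver has completed baseline by design.

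That leaves discontinuation as the only retention measure, and the feasibility study shows that people can stay in without returning questionnaires. At stake is power for the primary outcome: the pilot can be passed on all three criteria while 18-week completion runs below the level the 110 was built on.

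**Working it through.** **1. Reproduce the plan's figures.** Inputs (Power analysis): f² = 0.15, alpha 5% (taken as two-sided; the article does not say), 80% power. Test of one regression coefficient by the noncentral F distribution with 1 and N - k - 1 degrees of freedom and noncentrality f² × N.

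- N = 55, k = 1 predictor: power 0.805. With k = 4 predictors: 0.804. The 55 is reproduced.
- 55 / (1 - 0.5) = 110. The 110 is reproduced.

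Neither number is wrong. Together they mean that completion must be at least 55/110 = 50%, with no slack.

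**2. Power if completion is lower.** Same formula, 110 randomized, k = 1:

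| 18-week completion | Analysed | Power |
|---|---|---|
| 50% | 55 | 0.805 |
| 45% | 50 (49.5 rounded) | 0.765 |
| 40% | 44 | 0.709 |
| 35% | 38 | 0.642 |

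**3. Discontinuation against completion in the feasibility study.** Discontinued: 9/32 = 28%. Did not complete: 16/32 = 50%. Difference: 7/32 = 22 percentage points. Of the 32 - 9 = 23 who had not discontinued, at least 23 - 16 = 7 returned no complete questionnaires. The discontinuation criterion was met, while completion sat exactly on its limit. The exact 95% confidence interval for 16/32 is 32% to 68%, so these data do not settle whether 50% is achievable.

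**4. What the pilot can see, and when.** Assume even accrual over the ten months in the Sample section: 110/10 = 11 caregivers a month.

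- 30 randomized: 30/11 = 2.7 months.
- Pilot read one month later: 3.7 months.
- First caregiver reaches 18 weeks: 4.1 months.

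So no follow-up questionnaire is due when the pilot is read. Under slower accrual a few might be, but the listed analysis would not use them.

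**5. When completion in the same 30 could be read.** 2.7 + 4.1 + 0.5 (two weeks, to the second reminder) = 7.3 months. By then about 11 × (7.3 - 4.1) = 35 caregivers have reached week 18, and 110 - 35 = 75 have not.

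**6. Would a hard 50% trigger on 30 caregivers work?** Exact binomial probability of fewer than 15 completers out of 30:

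| True completion | Probability of falling below 15 |
|---|---|
| 55% | 0.23 |
| 50% | 0.43 |
| 45% | 0.64 |
| 40% | 0.82 |

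A hard trigger would misfire 43% of the time at exactly the planned rate, and would miss true completion of 45% in 36% of cases. The count is informative as an estimate but poor as a pass/fail rule. For example, 15/30 has an exact 95% interval of 31% to 69%.

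**The case against.** **The feasibility gap does not transfer.** A reader might infer that the trial's endpoint loss will exceed its discontinuation by 22 points. The documents do not support that. The 16/32 counts everyone who consented, with no described requirement to complete a questionnaire first, whereas the trial randomizes only those who have completed baseline. The battery has also been shortened since, by dropping a fatigue scale after caregivers found it too long. And the gap rests on seven people: if all who discontinued were also non-completers, the exact 95% interval for 7/32 is 9% to 40%. This objection stands in full. What survives is only that discontinuation and non-completion are different quantities.

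**Non-response is not invisible.** A reader might also infer that the trial would learn of poor completion only after most outcomes were lost. The Data collection section has reminders going to non-responders one and two weeks after each follow-up request, so non-response can be seen as it accrues. What is missing is a planned look at it and a planned response, not the information.

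**A stop/go gate has to be early.** Completion could not have been a one-month criterion, and a stopping decision at about month 7.3 of a ten-month recruitment would be of little use. This is right, and is a reason to leave the one-month read alone.

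**The 50% is an upper bound, and multiple imputation is planned.** The article allows for attrition up to 50%, so completion may well be better. But the bound is an expectation that the pilot does not test. Imputation keeps caregivers in the intention-to-treat analysis without restoring the endpoint information that the 55 counts on.

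**Conclusion.** The point holds as a gap in what the pilot checks. The pilot can pass while 18-week completion is below the 50% that the 110 requires; nothing in the article shows that this will happen. The loss is moderate: power falls from about 0.80 to about 0.77 at 45% completion and about 0.71 at 40%.

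These figures rest on the article's own effect size, a two-sided 5% test of one coefficient, and the 55 being observed endpoints. The timing rests on even accrual. The sample-size arithmetic itself is correct, and the one-month gate is reasonable for what it covers. The change is worth making because it is cheap and protects the rate on which the stated power depends.

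**What to change.** 1. **Keep the one-month stop/go read unchanged.**
2. **Add a non-stopping count of 18-week Preparedness for Caregiving Scale completion**, pooled over arms, as the first 30 caregivers pass that assessment (about month 7.3 at even accrual). Report it with its confidence interval against 50%, not as a hard trigger, given the error rates above.
3. **In both arms, offer any caregiver still silent after the second 18-week reminder a form holding only the 8-item primary scale.** This applies from the start and does not wait for the count. State that these responses count as observed primary-outcome data.

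The cost is one count from the existing data collection tool and the set-up of a short form. No further caregivers are needed, and there is no alpha cost, because no outcome is compared between arms. The downside is that secondary outcomes stay missing for those who use the short form, most of whom would otherwise give no data. How many non-responders the short form would recover is unknown; the documents give no figure.
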